### Statistical analysis plan

The primary analysis for estimating the treatment effect between MDA, fMDA, and control HFCAs for primary outcome one (parasite prevalence) and two (parasite infection incidence rates) will be based on intention to treat at the individual level for infections measured by RDT and PCR. The analysis of parasite prevalence will use a logistic or log binomial model, while the analysis for infection incidence will use a Poisson or negative binomial model. Models will include a random intercept at the HFCA level (randomization unit), fixed effect for intervention exposure, time period (pre- and post-intervention), plus other potential confounding factors. Standard errors will be estimated, with the addition of repeated measures among individuals.

Data for total and confirmed OPD and IPD malaria case incidence (outcome three) among all ages will be analyzed on an intention-to-treat basis. Routine data on case counts will be analyzed using a Poisson or negative binomial model, with random intercepts at the HFCA level. The models will include a fixed effect for study arm and time period (pre- and post-intervention), plus other potential confounding factors.

Differences in prevalence measures (RDT positivity) at each round will be assessed using an *X*^2^ test, as well as logistic regression models to account for potential confounding factors, on an intention-to-treat basis. Logistic models will include a random intercept for HFCA, as well as fixed effects for other potential confounding factors. Trends in parasite prevalence across rounds, with the inclusion of the control group, will then allow rapid assessment of the effect of the fMDA and MDA interventions over time, after removing the seasonality effect.

Standard methods for collecting cost data for the specific components of the work will be used to then summarize intervention costs. Cost-effectiveness calculations will be undertaken utilizing cost data collected as above, as well as the findings of the study evaluation on the effectiveness of the intervention. The primary cost-effectiveness outcome will be the calculation of the incremental cost effectiveness ratios (ICERs) comparing the cost-effectiveness of MDA to the standard of care, and the ICER of fMDA alone versus standard of care. Secondary outcomes will include the ICER of MDA versus fMDA alone, and the stratified analysis of all three previously listed outcomes by high and low prevalence settings. Further details of the cost and cost-effectiveness analysis are presented in the Additional file 1.

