#### Stratification

As the impact of the MDA and fMDA interventions are expected to vary across malaria transmission strata, the 60 HFCAs included in the study have been stratified into high and low transmission strata. To do this, parasite prevalence in each HFCA was estimated with a kriged continuous surface of parasite prevalence from data from the baseline 2014 parasite survey. Catchments were then ranked from highest to lowest parasite prevalence. The top 30 HFCAs were included in the high transmission strata, while the bottom 30 were included in the low transmission strata; the resulting cut point between the high and low transmission strata was approximately 10 % parasite infection prevalence.

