### Randomization sequence generation and allocation concealment

Pre-existing maps of HFCAs were used to classify households as belonging to a specific HFCA, which serve as the unit of randomization. To ensure balance across large and small HFCAs, which could potentially affect the quality of program implementation and other related unobserved confounding factors, HFCAs were characterized as having either a large or small population catchment size. This classification was based on a cut-point obtained from the mean population catchment size across the 60 HFCAs. Within the high and low transmission strata and the large and small population catchment size classifications, the random allocation rule will be used to assign HFCAs to the fMDA-DHAp, MDA-DHAp, or control group. As a result of this process and the stratification outlined above, the 60 total HFCAs are split into 10 HFCAs per treatment group (MDA, fMDA, and control) in the high transmission strata (n = 30 HFCAs), and 10 HFCAs per treatment group (MDA, fMDA, and control) in the low transmission strata (n = 30 HFCAs).

After allocation, the appropriate intervention will be implemented in the entire catchment area according to treatment group assignment. Allocation of study arms will not be blinded to the deliverers of the intervention or to the main investigators, as delivery of the intervention precludes the possibility of allocation concealment. However, data collectors in the follow-up parasite prevalence survey, as outlined below, will be blinded to allocation. All primary analyses will also be blinded to analysts by the use of concealed code for the study arm variables in the final dataset.

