### Primary outcome measures

Primary outcomes used to measures the impact of the MDA-DHAp and fMDA-DHAp interventions, as compared to a control of standard of care, are:Parasite prevalence during the high transmission season among children < six-years-old: defined as the proportion of children < six-years-old (≥three months to < six-years-old) with *P. falciparum* infection (based on both RDT and PCR) out of all children < six-years-old tested within the 2014 and 2015 cross-sectional parasite surveys.*P. falciparum* infection incidence rate among individuals ≥ three-months-old*:* defined as the number of individuals ≥ three-months-old with a new *P. falciparum* infection (based on PCR) divided by the total person-time observed among a cohort of individuals ≥ three-months-old followed up on for a 12-month-period.Total and confirmed outpatient (OPD) malaria case incidence and inpatient (IPD) malaria case incidence among all ages: defined as the number of OPD and IPD malaria confirmed and suspected cases per person per year, as ascertained from the routine rapid reporting system; facility catchment population size estimates will be used for the exposure denominator.RDT positivity: defined as the proportion of all individuals tested by RDT at each round of the fMDA and MDA interventions (and among a contemporaneous sample in the control group), with a positive RDT, among the population of individuals ≥ three-months-old.

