### Routine health information on confirmed and suspected malaria cases

Data on aggregate clinical and laboratory confirmed malaria cases and total outpatients seen are submitted on a weekly basis, through a standardized forma on data-enabled cell phones, using the District Health Information System 2 (DHIS2) rapid reporting system, from all 60 health facilities in the study area. Data from this source are accessible via a web server with password protection. This system was established in 2011 and 2012 and has been running in the catchment areas ever since. Time series data by facility week will be collated from this system to provide a passive incidence-based data set for evaluation of the impact of the MDA and fMDA interventions, as compared to a control of no mass treatment, on primary outcome three. Confirmed and total case counts will be standardized by the estimated mid-year populations of each HFCA.

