### Study timeline

Figure 5 shows the timeline for the major activities for the primary study of evaluating the impact of the MDA and fMDA interventions on reducing malaria morbidity. The study started with the randomization of HFCA in early 2014. The baseline parasite survey was conducted between April and May of 2014 during the peak malaria transmission season. The first MDA and fMDA rounds were conducted between November and December 2014, with round two scheduled for February 2015. The longitudinal cohort started at the same time as the first MDA and fMDA round in November 2014; the cohort will continue monthly follow-up through November 2015. Routine data on confirmed OPD malaria cases started in January 2014 and will continue through 2015. The follow-up parasite survey is scheduled to take place between April and May 2015, during the peak malaria transmission season.

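### The listed model terms leave out both randomisation factors, give the cohort no usable baseline, and do not define the pre/post treatment contrast

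*Protocol article*

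**What the plan says.** **Allocation.** Under Randomization sequence generation and allocation concealment: "Within the high and low transmission strata and the large and small population catchment size classifications, the random allocation rule will be used". That section justifies the size classes by a possible link between catchment size and quality of implementation. Under Stratification, the transmission strata come from a "kriged continuous surface of parasite prevalence from data from the baseline 2014 parasite survey".

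**Models.** Under Statistical analysis plan, for outcomes one (prevalence) and two (cohort incidence): "Models will include a random intercept at the HFCA level (randomization unit"), together with a "fixed effect for intervention exposure, time period (pre- and post-intervention), plus other potential confounding factors". For outcome three (facility case incidence): "The models will include a fixed effect for study arm and time period (pre- and post-intervention), plus other potential confounding factors". For outcome four (RDT positivity), the logistic model has an HFCA random intercept and unspecified confounders. No outcome has a named term for transmission stratum or catchment size.

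**Baseline data.** Outcome one is defined on children "tested within the 2014 and 2015 cross-sectional parasite surveys", so the 2014 survey is part of its outcome data. The Study timeline says: "The longitudinal cohort started at the same time as the first MDA and fMDA round in November 2014". Of the facility reporting system, the article says: "This system was established in 2011 and 2012 and has been running in the catchment areas ever since".

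**Level of comparison.** The Background, the sample-size sections and the Discussion frame the comparisons within high and low transmission. The Statistical analysis plan does not say whether models are fitted by stratum or pooled.

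**The concern.** Factors used to restrict the allocation belong in the primary model by design. Here they could enter only through an open reference to confounders. There are three separate consequences.

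1. **Strata.** If the strata are pooled without a stratum term, the high/low difference stays in the between-HFCA error. Catchment size is left out under either approach.
2. **Cohort.** A pre/post term is prescribed for an outcome that has no pre-intervention follow-up. It therefore cannot adjust for differences between HFCAs, and no other HFCA baseline is named although the 2014 survey covered all 60.
3. **Outcomes one and three.** Pre-intervention data are modelled, but the coefficient that represents the treatment effect is not defined. With only arm and period as main effects, which is the literal list for outcome three, the arm coefficient averages the pre- and post-intervention differences. For outcome one it is not stated whether exposure is coded as varying over time.

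The Discussion already calls the number of clusters less than ideal, and 60 is the maximum available. Covariate adjustment is therefore the cheapest remaining source of precision.

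**Working it through.** **Inputs, from the sample-size sections.** There are 10 HFCAs per arm and stratum, one-sided 5% and 80% power (the text calls the 5% a type two error; it is read here as the significance level).

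- Cohort, high stratum: 1.8 to 0.91 per person-year, 25 persons per HFCA, CV 0.50.
- Cohort, low stratum: 0.6 to 0.28, 27 persons per HFCA, CV 0.50.
- Prevalence: 30% to 18% (CV 0.31) and 10% to 4% (CV 0.41), 39 children per HFCA.

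**Step 1: reproduce the plan.** For rates, c = 1 + (1.645 + 0.842)² V/(λ0 − λ1)², with V = (λ0 + λ1)/y + k²(λ0² + λ1²).

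- High: V = 2.71/25 + 0.25 × 4.0681 = 0.108 + 1.017 = 1.125; c = 9.78.
- Low: V = 0.88/27 + 0.25 × 0.4384 = 0.0326 + 0.1096 = 0.1422; c = 9.59.

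The prevalence analogue gives 9.99 (high) and 10.00 (low). All four agree with the 10 clusters stated.

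**Step 2: between-HFCA share of the cohort variance.** High: 1.017/1.125 = 90%. Low: 0.1096/0.1422 = 77%.

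**Step 3: cohort power with a baseline covariate.** Power = Φ(√[9(λ0 − λ1)²/V] − 1.645), with the between-HFCA part multiplied by (1 − R²). R² is not in the documents; 25% is an assumption.

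| Stratum | V, R² = 0 | Power | V, R² = 25% | Power |
|---|---|---|---|---|
| High | 1.125 | 81% | 0.871 | 89% |
| Low | 0.142 | 82% | 0.115 | 88% |

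Is 25% plausible? The raw 2014 prevalence carries sampling error. In the low stratum, between-HFCA variance is (0.41 × 0.10)² = 0.00168 and sampling variance is 0.10 × 0.90/39 = 0.00231, so reliability is 0.42. In the high stratum the values are 0.00865 and 0.00538, so reliability is 0.62. An R² of 25% then needs a true correlation between 2014 prevalence and cohort incidence of √(0.25/0.42) = 0.77 (low) or √(0.25/0.62) = 0.64 (high).

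**Step 4: pooling without a stratum term.** Within-stratum HFCA variance averages (0.093² + 0.041²)/2 = 0.00517. The high/low difference adds ((0.30 − 0.10)/2)² = 0.0100. The ratio is 0.01517/0.00517 = 2.9.

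For a post-intervention comparison with 20 HFCAs per arm and a mean difference of 9 points ((12 + 6)/2), the SE is 2.56 points with the stratum term and 3.74 without it. Power on a t reference is 96% and 76% respectively. The 76% treats 3.74 as the real sampling spread. Because allocation is balanced by stratum, the real spread stays at 2.56, so the test would reject about 87% of the time under the alternative and about 0.8% under the null at a nominal one-sided 5%. On either reckoning the test is conservative and loses power.

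**Step 5: arm plus period without an interaction (outcome three).** This is an illustration. Take the Study timeline's routine data from January 2014 through 2015, with November 2014 as the change point: 10 months before and 14 after. Assume a flat monthly rate and a true halving after the change point. With main effects only, the arm ratio is set by the arm totals: (10 + 14 × 0.5)/24 = 0.71. A 50% reduction would be reported as about 29%, and a longer pre-period would dilute it further.

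**The case against.** The strongest reply is that an article summarises its analysis plan, and that the open reference to confounders can include both randomisation factors. The randomisation section itself links catchment size to unobserved confounding. That is fair as to intent. However, the article prints a term list, and design factors should be on it, not left for later selection.

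Several stronger readings are tempting but not supported:

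- **A reader might infer that every model ignores the 2014 baseline.** This is not so for outcomes one and three, where pre-intervention data and an HFCA intercept are in the model. What is missing there is the contrast.
- **A reader might combine the 2.9-fold variance with 10 against 10 HFCAs.** The two belong to different analyses. Within a transmission stratum that factor is constant and cannot inflate the error; pooled, there are 20 HFCAs per arm. The 2.9 also applies to a between-arm comparison of levels; a pre/post contrast within HFCAs would largely remove a stable stratum difference.
- **A reader might expect larger cohort gains, such as R² = 50%.** With raw prevalence, low-stratum reliability of 0.42 puts that out of reach even at perfect correlation.
- **A reader might infer a seriously liberal test from the missing small-cluster reference distribution.** The plan states no normal reference, and an article commonly leaves this to the full plan. On the plan's one-sided basis, a normal reference at 18 degrees of freedom would give about 5.9% instead of 5%.

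It is also true that cohort members are tested at enrolment. That gives infection status at one visit, not pre-intervention person-time, so it does not supply a pre-period for an incidence rate.

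**Conclusion.** The point holds as a specification gap that should be closed, not as an error in the sample size, which reproduces without any baseline covariate. Three parts stand on the text alone: neither randomisation factor is listed, the cohort's pre/post term has nothing to act on, and the treatment contrast for outcomes one and three is undefined.

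The size depends on assumptions. The cohort gain of 6 to 8 percentage points of power requires R² = 25%, which is demanding in the low stratum given the noise in the survey prevalence, the different age range and the IRS campaign between the two measurements. The pooling loss arises only if strata are pooled without a stratum term, which the article neither commits to nor rules out. The dilution for outcome three arises only if the listed terms are fitted literally.

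**What to change.** In the Statistical analysis plan section:

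1. Include catchment-size class as a fixed effect in every primary model.
2. State whether models are fitted within transmission stratum. If pooled, include transmission stratum and arm-by-stratum.
3. For the cohort, remove the pre/post term and add the HFCA's 2014 survey prevalence, or its pre-intervention case incidence, as a covariate.
4. For outcomes one and three, define the treatment effect as the arm-by-period contrast. Do not also enter 2014 prevalence as a covariate for outcome one, where it is already outcome data.
5. As a secondary suggestion, name a t reference with HFCA-based degrees of freedom, or a permutation test within the randomisation cells.

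All the variables are already collected. The cost is a change of wording and two or three HFCA-level degrees of freedom, out of 18 for a two-arm comparison within a stratum.

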### Study design

A CRCT will be used to evaluate the impact of two rounds of the MDA-DHAp or fMDA-DHAp (the two intervention arms) at reducing malaria parasite infection prevalence and incidence, as well as malaria-related morbidity, compared to a control group receiving standard of care. Communities, or clusters, are defined by HFCAs and serve the unit of randomization. A total of 60 health facilities and their catchment areas are included in the study.

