#### Rapid diagnostic test positivity during campaign rounds

It is estimated based on the population sizes of the MDA and fMDA HFCAs, a sample size exceeding 50,000 individuals aged three-months-old and older in each group (approximately 5,000 per HFCA) will be achieved. As described above, a sample size of 750 individuals aged three-months-old and older in the cohort in the control HFCAs will provide contemporaneous measure of RDT positivity in areas without intervention rounds (n = 375 individuals in the high transmission strata and 375 individuals in the low transmission strata). This sample size in areas of high transmission will provide 80 % statistical power to detect a 33 % difference (an absolute decrease from 30 to 20 %; odds ratio of 0.58) in RDT positivity between the control group and either of the MDA groups, assuming a baseline prevalence of 30 %, a CV = 0.31, 10 HFCAs in each treatment group, and a probability of committing a type two error of 5 % (one-tailed test). This sample size in areas of low transmission will provide 80 % statistical power to detect a 50 % difference (an absolute decrease from 10 to 5 %; odds ratio of 0.47) in RDT positivity between the control group and either of the MDA groups, assuming a baseline prevalence of 10 %, a CV = 0.41, 10 HFCAs in each treatment group, and a probability of committing a type two error of 5 % (one-tailed test).

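### RDT positivity, a primary outcome, is given an X² test with no stated cluster adjustment beside a cluster-aware model, and the plan does not say which of the two decides

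*Protocol article*

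**What the plan says.** The Study design section fixes the unit of allocation: "Communities, or clusters, are defined by HFCAs and serve the unit of randomization". The Primary outcome measures section lists as its fourth item "RDT positivity: defined as the proportion of all individuals tested by RDT at each round of the fMDA and MDA interventions", with a contemporaneous control sample as comparator.

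For this outcome the Statistical analysis plan names two methods in one sentence. The first: "Differences in prevalence measures (RDT positivity) at each round will be assessed using an" X² test. The second follows directly: "as well as logistic regression models to account for potential confounding factors, on an intention-to-treat basis". The next sentence gives the second method its cluster term: "Logistic models will include a random intercept for HFCA, as well as fixed effects for other potential confounding factors". Nothing comparable is said of the X² test.

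The sample-size paragraph on RDT positivity expects "a sample size exceeding 50,000 individuals aged three-months-old and older in each group (approximately 5,000 per HFCA") in the intervention arms and a control sample of "n = 375 individuals in the high transmission strata and 375 individuals in the low transmission strata". Its assumptions for the high stratum are a 30% baseline and "a CV = 0.31, 10 HFCAs in each treatment group"; for the low stratum they are a 10% baseline, a CV of 0.41 and again 10 HFCAs per group.

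**The concern.** A standard X² test takes each person tested as an independent observation. Here whole HFCAs are allocated, and the sizing paragraph for the same outcome assumes that prevalence varies between HFCAs within an arm. The sizing and the first-named test therefore rest on incompatible assumptions.

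The consequence is large because many people are tested in few HFCAs. With about 5,000 tests per intervention HFCA, sampling error within those HFCAs almost vanishes, and what remains is the chance draw of which 10 HFCAs fell into the arm. A test that leaves this component out reads ordinary differences between HFCAs as differences between arms.

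Outcomes one to three are given only random-intercept models in the same section. Outcome four alone also gets a test without a cluster term. Since neither method is given precedence, the two can disagree on a primary outcome and the plan does not settle which result counts.

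**Working it through.** **Inputs** (all from the sample-size paragraph on RDT positivity)
- HFCAs per arm within a stratum: 10.
- Control tests per stratum: 375, that is 37.5 per HFCA.
- Intervention tests: about 5,000 per HFCA, so 50,000 over 10 HFCAs.
- High stratum: p = 0.30, CV k = 0.31. Low stratum: p = 0.10, k = 0.41.
- Error rate: 5% one-tailed. The text labels it a type two error; it is used here as the significance level.

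**1. The plan's own figures.** The unmatched Hayes–Moulton formula for proportions is

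c = 1 + (z_α + z_β)² [p0(1−p0)/m0 + p1(1−p1)/m1 + k²(p0² + p1²)] / (p0 − p1)²

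For the parasite survey (39 children per HFCA, one-sided 5%, 80% power) it gives c = 9.99 in the high stratum (30% to 18%) and 10.00 in the low stratum (10% to 4%), against the 10 available. The survey sizing reproduces, so the formula and the CVs are read as intended.

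For RDT positivity (m0 = 37.5, m1 = 5,000) it gives c = 12.21 (30% to 20%) and 12.16 (10% to 5%). With 10 HFCAs the power is about 72% in each stratum, or about 76% without the added 1, against the stated 80%. The stated odds ratios of 0.58 and 0.47 do reproduce. The shortfall in power is a separate matter and does not enter the steps below.

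**2. Variance of the difference in proportions when there is no effect**
- Assumed by the X² test: V_naive = p(1−p)(1/375 + 1/50,000)
- Under the protocol's CV: V_true = V_naive + k²p²(1/10 + 1/10)

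High stratum:
- V_naive = 0.21 × 0.00268667 = 0.000564
- added term = 0.0961 × 0.09 × 0.2 = 0.001730
- R = V_true/V_naive = 0.002294/0.000564 = 4.07

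Low stratum:
- V_naive = 0.09 × 0.00268667 = 0.000242
- added term = 0.1681 × 0.01 × 0.2 = 0.000336
- R = 0.000578/0.000242 = 2.39

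**3. Actual false-positive rate at a nominal 5%.** Two-sided: 2[1 − Φ(1.96/√R)]. One-sided: 1 − Φ(1.645/√R).

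| Stratum | R | Two-sided | One-sided |
|---|---|---|---|
| High (30%, CV 0.31) | 4.07 | 33.1% | 20.7% |
| Low (10%, CV 0.41) | 2.39 | 20.5% | 14.4% |

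**4. Check by simulation.** A beta-binomial simulation with 20,000 runs gave two-sided rates of 32.8% and 20.6% for the X² test. A Welch t-test on the 10 versus 10 HFCA proportions gave 4.9% and 5.2%.

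**5. Sensitivity (two-sided)**
- CV from 0.10 to 0.50: 9% to 51% in the high stratum, 6% to 26% in the low stratum. At CV 0.20, below both protocol values: 19% and 9%.
- Control sample reduced to 25 per HFCA (37.5 less one third, taking the protocol's 33% cohort loss as already complete): 26% and 16%.
- If the 50,000 were spread over both strata (25,000 per arm per stratum), R = 1 + 0.001730/[0.21 × (1/375 + 1/25,000)] = 4.04 in the high stratum and 1 + 0.000336/[0.09 × (1/375 + 1/25,000)] = 2.38 in the low stratum, so the result hardly moves.

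**The case against.** The strongest reply is that the plan already contains a valid analysis. The sentence that names the X² test also names logistic models, and these carry a random intercept for HFCA. The Discussion says that impact will be assessed within random-effect regression models, and the Statistical analysis plan reads the effect on RDT positivity from trends across rounds with the control group included. This stands. A reader might infer that the whole analysis of outcome four ignores the randomisation by HFCA, so that its error rate is 20–33%. The documents do not support that: the inflated rate belongs to one of two named methods.

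Other parts of the reply also stand:
- The protocol does not say that the X² test is unadjusted. That is the ordinary meaning of the term, but it is an assumption here.
- The sizing is one-tailed, and on that basis the rates are 21% and 14%.
- The same CVs appear in the survey sizing in young children, whereas this outcome covers everyone aged three months and older. The protocol nevertheless adopts them for this outcome.
- A reader might also apply the X² test to MDA against fMDA, where the same formulas give error rates of 84–89%. The Sample size section plans each intervention against control, so that figure is no measure of the planned comparisons.

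Two parts do not remove the point. First, the RDT precedes the offer of DHAp, so round one is not a test of a campaign effect. But a test at each round would then report spurious imbalance at round one too often, and this would colour the reading of the later trend. Second, the abstract names only prevalence and incidence among the primary outcomes. But the Primary outcome measures section lists four, and the Sample size section refers to four primary outcomes.

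**Conclusion.** The point holds in a limited form. The plan attaches to a listed primary outcome a test with no stated cluster adjustment, does not mark it as descriptive, and does not say that the mixed model beside it takes precedence. If followed as written with a standard X² test, the plan yields an invalid p-value for control against either intervention arm, with a false-positive rate about three to seven times the nominal 5%, depending on stratum and sidedness.

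This rests on three assumptions: an ordinary Pearson test, the protocol's CVs taken as within-stratum values, and the planned numbers tested. The direction does not depend on the exact CV: in both strata the rate is above 5% at every value tried. The random-intercept model is unaffected, and so are outcomes one to three, which have no such test.

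**What to change.** In the Statistical analysis plan, delete the X² test for RDT positivity, replace it with a cluster-adjusted version, or state that it is descriptive only. In the same sentence, name one deciding analysis for outcome four: the logistic model with the HFCA random intercept that is already planned, or a t-test on the 10 versus 10 HFCA-level proportions within each stratum.

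The cost is one sentence and p-values less favourable than the X² test would give. No new data are needed, and the odds ratios and intervals from the mixed model do not change.
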